### Sample size {14}

The sample size calculation to conduct a fully powered trial was informed by a meta-analysis of 22 randomised controlled trials evaluating digital psychological interventions in LMICs [18]. The meta-analysis found an average effect size of Hedge’s *g* = 0.60 in favour of the digital intervention, *g* = 0.53 for interventions addressing substance use, and *g* = 0.43 when an active control group was used. We therefore assumed a more conservative effect size of *g* = 0.40 in favour of mhGAP-Remote to calculate the sample size. This translates to a true mean difference of 2.4 points in the AUDIT score change between treatment arms from baseline to 8 weeks (range 6 to 16 weeks) follow-up. We assumed a pooled standard deviation (SD) of 6 [38, 39]. Thus, with an allocation ratio of 1:1, a sample size of 99 participants in each treatment arm is required for statistical power of 80% and a two-sided type I error of 0.05. Prior clinical trials by the study team within similar settings and populations (clinic-based recruitment, unhealthy alcohol use) indicate a roughly 10% attrition rate [36, 40]. However, we chose a more conservative estimate of 20% attrition resulting in a total sample size of *N*_planned_ = 248 (*n* = 124 per treatment arm). Prior to recruiting participants into the fully powered trial, we plan to pilot the study procedures with up to 10 participants.

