## Data collection and management

### Plans for assessment and collection of outcomes {18a}

Once a participant consents to study participation, self-reported assessments are collected in REDCap via interview. Trained research assistants collect dry blood spots (DBS) to assess for PEth, medical records are accessed to collect data on liver enzymes and HIV viral load (subsample with HIV only) and data is entered into REDCap. If participant medical records indicate a test result of more than 30 days old, research assistants escort participants to the medical staff to have new tests taken. All primary, secondary, and exploratory outcomes are collected at all timepoints (see {12} for description of outcomes).

Data quality is promoted by training assessors on adherence to data collection protocols and rules of trial conduct, including proper data collection techniques. Additionally, all members of the study team have completed formal human subjects research training in social and behavioural sciences, which is consistent with Good Clinical Practice. The AUDIT assessment is recorded and independent raters code randomly selected recordings to determine level of performance and adherence to assessment protocols.

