## Statistical methods

### Statistical methods for primary and secondary outcomes {20a}

Primary and secondary analyses will follow CONSORT guidelines and intention-to-treat principles (i.e., all participants will be analysed according to their randomisation condition, regardless of whether they complete the assigned treatment). A flowchart will describe the inclusion and follow-up of participants by study arm. Baseline characteristics will be described by study arm with summary statistics, such as mean and standard deviation for normally distributed data, median and interquartile range for non-parametric continuous data, or number and percentage in the case of categorical indicators. No formal testing between arms will be performed. Outcomes will be described by arm using summary statistics.

For the primary analysis, we will employ a linear regression model on the outcome of difference in mean AUDIT scores from baseline to 8 weeks follow-up (range 6–16 weeks) using the arm allocation, stratification factors, and site (if sample size per site allows). Only participants who have an AUDIT score at the 8-week assessment will be included in this analysis. Superiority of mhGAP-Remote will be demonstrated if the lower bound of the 95% Wald confidence interval of the difference between the arms is superior to zero.

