
For secondary analyses, we will evaluate changes from baseline in (1) AUDIT scores at the 20- and 32-week follow-ups and (2) changes in the biomarker PEth at 8-, 20-, and 32-week follow-ups. We will employ multilevel mixed effects regression models and control for clustering of variance within individuals over the repeated measures. For the AUDIT, we will use a normal distribution and identity link. For PEth, we will evaluate the data’s distribution and choose a suitable regression model and link function for analysis. Models will be adjusted for the arm allocation, stratification factors, and site (if sample size per site allows). We will report adjusted mean differences between treatment arms. Furthermore, we will compare the maintenance of “recovery” and clinically significant and reliable change at the 20- and 32-week follow-up assessments across the treatment arms.

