### Methods in analysis to handle protocol non-adherence and any statistical methods to handle missing data {20c}

Previous clinical trials conducted by the study team have recorded less than 10% attrition [36, 40]. In the power analysis for the present study, we have used a conservative estimate of 20% attrition. Participants who drop out, who fail to attend a study assessment, or who are lost to follow-up will not be replaced by new participants, as we have accounted for this in the sample size estimate. Missing baseline and outcome data will be summarised by study arm and reported in the CONSORT. If attrition is higher than anticipated, multiple imputation will be used to impute the AUDIT score [50], and primary and secondary analyses will be conducted with the imputed datasets.

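### Read literally, the secondary AUDIT mixed model leaves out the 8-week score, which can bias the 20- and 32-week comparisons if later dropout depends on that score differently in the two arms

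*Protocol article*

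**What the plan says.** All of the following is in the protocol article.

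- Section {20a}, secondary analyses, AUDIT: "we will evaluate changes from baseline in (1) AUDIT scores at the 20- and 32-week follow-ups".
- The same sentence, for PEth: "2) changes in the biomarker PEth at 8-, 20-, and 32-week follow-ups".
- The model for both: "We will employ multilevel mixed effects regression models and control for clustering of variance within individuals over the repeated measures".
- The covariates: "Models will be adjusted for the arm allocation, stratification factors, and site (if sample size per site allows". The 8-week AUDIT is not among them.
- The 8-week AUDIT is the primary outcome and has its own linear regression, restricted as follows: "Only participants who have an AUDIT score at the 8-week assessment will be included in this analysis".
- Section {18a}: "All primary, secondary, and exploratory outcomes are collected at all timepoints". The 8-week AUDIT is therefore on file for people who are lost afterwards.
- Section {20c}: "If attrition is higher than anticipated, multiple imputation will be used to impute the AUDIT score". In that case both the primary and the secondary analyses use the imputed data. The imputation variables are not named.
- Section {14}, on the anticipated level: "we chose a more conservative estimate of 20% attrition resulting in a total sample size of" 248. Sections {14} and {20c} also cite the team's earlier trials, with attrition of roughly 10% or less.

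**The concern.** A likelihood-based mixed model allows for dropout that depends on earlier observed outcomes only if those outcomes are in the model. With outcome rows at weeks 20 and 32 only, someone last seen at week 8 has no row. Arm, sex, age stratum and site say nothing about how that person was drinking at week 8. Yet the 8-week AUDIT is likely to be a strong predictor of the later scores, and plausibly of later attendance.

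The 20- and 32-week AUDIT results are what will show whether an 8-week effect lasts. Participants know their arm, and the arms differ sharply in contact: four to six in-person sessions against one session plus SMS. A link between week-8 drinking and later attendance could therefore differ by arm. If it does, the arm difference among those still seen is shifted, although the trial holds the data that explain the dropout.

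**Working it through.** **The plan's own figure.** The article states no figure for the secondary model. Its sample size reproduces: n per arm = 2 × (1.960 + 0.842)² × 6² / 2.4² = 98.1, so 99; 99 / 0.80 = 123.75, so 124 per arm and 248 in total. Nothing below changes this.

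**Inputs from the article.** 124 per arm, SD 6, planned difference 2.4 points, 20% attrition allowed for, roughly 10% seen in earlier trials.

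**Assumptions not in the article.** Correlation ρ = 0.6 between change scores at different visits; 10% lost at random before week 8; later loss of 5% or 10%; true difference 2.4 at each visit; loss logistic in the standardised 8-week change with slope b = 0.7 per SD.

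**Total loss against the 20% allowance.**
- 5% later: 1 − 0.90 × 0.95 = 14.5%
- 10% later: 1 − 0.90 × 0.90 = 19.0%
- 15% later: 1 − 0.90 × 0.85 = 23.5%, above the allowance

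**Approximate bias when all later loss falls before week 20.** Losing a fraction p with slope b shifts the mean standardised 8-week score of those who remain by about b × p. A fraction ρ of that shift carries to week 32. The bias contributed by one arm is therefore about ρ × SD × b × p = 0.6 × 6 × 0.7 × p = 2.52p.

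- *Dependence in one arm:* 2.52 × 0.05 = 0.13; 2.52 × 0.10 = 0.25.
- *Opposite dependence in the two arms:* twice that, 0.25 and 0.50.
- *Equal dependence:* the two shifts cancel except that the arms lose different fractions. The Remote mean is 2.4/6 = 0.4 SD lower, so its log-odds of loss are 0.7 × 0.4 = 0.28 lower. A 10% rate becomes 7.75% and a 5% rate 3.83%. The bias is 2.52 × 0.0225 = 0.06 and 2.52 × 0.0117 = 0.03, towards no difference.

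**Simulation under the same assumptions** (ranges reflect separate runs and how the 8-week score was standardised):

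| Dependence on the 8-week score | 5% later loss | 10% later loss |
|---|---|---|
| One arm only | 0.12 to 0.15 | 0.23 to 0.26 |
| Opposite in the two arms | 0.26 to 0.29 | 0.51 to 0.58 |
| Equal in both arms | 0.02 to 0.04 | 0.05 to 0.07 |

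With the 8-week score in the model, the bias is within 0.03 in the one-arm and opposite settings, and within 0.02 for equal dependence.

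**If loss is split evenly before and after week 20.** Even the two-visit model uses the 20-week score of those lost later, so the bias roughly halves. At 5% later loss, simulation gives 0.07 to 0.08 (one arm) and 0.13 to 0.14 (opposite).

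**Scale.** At 5% later loss about 124 × 0.90 × 0.95 = 106 per arm remain, and SE = 6 × √(2/106) = 0.82. At 10%, about 100.4 per arm remain and SE = 0.85.

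**Sensitivity to the slope.** With slope 1 per SD, correlation 0.5 or 0.7, no loss before week 8 and a 10% base rate (total loss 10% to 13%), the bias across weeks 20 and 32 is 0.24 to 0.53 (one arm) and 0.60 to 1.00 (opposite). With equal dependence it is 0.10 to 0.19 under a 2.4-point effect and within 0.03 under no effect. With week 8 in the model it is within 0.06 throughout.

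**Precision under random loss.** Simulated SE without and with week 8: 0.805 and 0.801 at 5% (0.5% smaller), 0.850 and 0.837 at 10% (1.5%), 0.888 and 0.863 at 15% (2.8%).

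**The case against.** - **The list may be a list of endpoints.** It matches the Secondary outcomes section, where AUDIT appears at 20 and 32 weeks and PEth at all three visits. Week-8 AUDIT is absent because it is the primary outcome, so the contrast with PEth may show only the endpoint hierarchy. A model on all AUDIT visits that reports weeks 20 and 32 would fit the text. This stands: a reader might infer that the plan excludes the 8-week score, but the article never says so.
- **Model rows are often left to the analysis plan.** True, and so this is not called an error or an omission. The article does, however, name visits directly before the model, and the literal reading gives the weaker analysis.
- **Dropout related to 8-week drinking need not bias the comparison.** This stands. Equal dependence leaves under 0.1 points at slope 0.7. Material bias needs dependence that differs by arm. The open-label design makes that plausible, but nothing in the article shows it. A reader might infer that the 20- and 32-week results are biased; the documents support only that they can be.
- **Imputation may cover it.** At 15% later loss the bias would be 0.32 to 0.40 (one arm) or 0.74 to 0.81 (opposite). Total loss is then 23.5%, where imputation would start, so those figures are left out of the conclusion. If the anticipated level means the team's record of about 10%, even 14.5% and 19% would trigger it. On the 20% reading they would not. Imputation helps here only if the 8-week score is used in it, and the article does not say.
- **The simple comparison overstates the bias.** This stands in part: the size halves if loss is spread around week 20, and the lower ends below allow for that.

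**Conclusion.** The point holds as a weakness of wording that can be removed at no cost, not as a demonstrated bias. On the literal text, participants last seen at week 8 drop out of the secondary AUDIT model and the 8-week score enters nowhere.

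Under the stated assumptions with 5% to 10% later loss, the 32-week arm difference is biased by about 0.1 to 0.25 points for one-arm dependence and about 0.15 to 0.55 for opposite dependence. The upper ends are about 10% (0.25/2.4) and 23% (0.55/2.4) of the planned effect, or roughly 0.3 and 0.65 standard errors (0.25/0.85 and 0.55/0.85). The direction depends on who leaves which arm. A steeper slope gives more, and equal dependence gives little or nothing. Only secondary results are touched.

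**What to change.** In section {20a}, state that the AUDIT mixed model is fitted to the changes from baseline at weeks 8, 20 and 32 together, with the arm difference estimated separately at each visit. The by-visit estimation matters: with a single arm effect, adding week 8 would mix the primary endpoint into the secondary estimate. Report the 20- and 32-week differences as the secondary results, label the model's 8-week estimate supportive, and leave the primary linear regression as it is.

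The cost is a sentence. No data, visits or participants are added, and precision improves slightly (about 1% to 3%). The change does not help participants lost before week 8, who have no follow-up score under either version. If the full protocol or analysis plan already fits all three visits, aligning the article's wording is enough.

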### Interim analyses {21b}

We do not plan to conduct interim analyses as we do not have any safety or efficacy concerns about this trial.

### Methods for additional analyses {20b}

As part of the main analyses, we do not plan to carry out additional subgroup or adjusted analyses. However, we plan to conduct exploratory subgroup analyses by sex for the primary outcome. The analysis will be performed as the main primary outcome analysis and include an interaction term between sex and treatment allocation. If the interaction term is found to be significant, effect estimates will be summarised by sex. This will allow us to evaluate whether the intervention was differentially effective for men versus women. Given the established importance of sex and gender in health research [49], it is of a priori importance to us to evaluate possible differential effects of the intervention for men versus women. Additional analyses (e.g. mediator and moderator analyses, or analyses of baseline data) will also be conducted in an exploratory fashion rather than as part of main analyses described in this protocol. Such exploratory analyses will be disseminated in separate publications from main analyses.

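### Sex-specific effects are to be shown only after a significant sex-by-arm interaction, a test with roughly 20–35% power for an interaction as large as the design effect; estimates and intervals should be reported whatever the p-value

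*Protocol article*

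**What the plan says.** Under Methods for additional analyses {20b}, the protocol article sets the sex analysis apart from the main analyses: "we plan to conduct exploratory subgroup analyses by sex for the primary outcome". The model is fixed: "The analysis will be performed as the main primary outcome analysis and include an interaction term between sex and treatment allocation". Reporting is then made conditional: "If the interaction term is found to be significant, effect estimates will be summarised by sex". The section also gives the reason for asking: "it is of a priori importance to us to evaluate possible differential effects of the intervention for men versus women".

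The Sample size {14} section addresses only the overall comparison. It assumes a difference in AUDIT change of 2.4 points and an SD of 6, and concludes that "a sample size of 99 participants in each treatment arm is required for statistical power of 80% and a two-sided type I error of 0.05". With 20% attrition this becomes 248 randomised. No interaction size, power for an interaction or expected share of women is stated. Sequence generation {16a} makes sex a stratification factor, so the arms should be close to balanced within each sex.

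**The concern.** A significance condition on display suits a test that has a good chance of detecting what matters. Here the test is a by-product of a trial sized for the main effect, and an interaction is estimated with about twice the standard error of that effect. Two things follow if the rule is applied literally.

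- In the likeliest case the interaction is not significant. The effects in men and in women, and the width of their intervals, are then not shown. A reader cannot tell whether the data argue against a sex difference or are too imprecise to say.
- When the condition is met, the estimates shown have been selected for differing widely, so the apparent sex difference tends to be too large.

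Both fit poorly with a question that the protocol itself singles out as important. At stake is the usefulness of a stated exploratory analysis. The primary inference, the error rate and the sample size are not affected.

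**Working it through.** **Inputs from the Sample size {14} section.** Difference 2.4 ("This translates to a true mean difference of 2.4 points in the AUDIT score change between treatment arms"); SD 6 ("We assumed a pooled standard deviation (SD) of 6"); two-sided 5% level; 80% power; "with an allocation ratio of 1:1"; 20% attrition, with about 10% seen in the team's earlier trials.

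**Assumptions, because the documents are silent.** A true interaction of 2.4 points, equal to the design effect; women making up 20% to 50% of those analysed; arms balanced within sex; SD 6 in both sexes; normal approximation. If the sexes are equal in number, a 2.4-point interaction means, for example, a benefit of 3.6 points in one sex and 1.2 in the other, averaging 2.4. That is a material difference.

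**Step 1: the plan's own figure.** n per arm = 2 × 6² × (1.96 + 0.8416)² / 2.4² = 98.1, rounded up to 99. Power at 99 per arm is 80.4% by the normal approximation and 80.0% by the noncentral t. 99 / 0.8 = 123.75, hence 124 per arm and 248 in total. The stated sample size reproduces.

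**Step 2: standard error of the interaction.** SE = 6 × √(4/n_women + 4/n_men).

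- 198 analysed, 99 women and 99 men: 6 × √(8/99) = 1.71. For comparison, the main effect has SE 6 × √(2/99) = 0.85, half as large.
- 198 analysed, 20% women (39.6 and 158.4): 6 × √(0.1010 + 0.0253) = 2.13.

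**Step 3: what the condition demands.** With equal sexes at 198, the estimated between-sex difference must exceed 1.96 × 1.706 = 3.34 points, more than the whole 2.4-point design effect. With 20% women it must exceed 1.96 × 2.132 = 4.18 points.

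**Step 4: power for a 2.4-point interaction.** Power = Φ(2.4/SE − 1.96) + Φ(−2.4/SE − 1.96).

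| Analysed | 50% women | 40% | 30% | 20% |
|---|---|---|---|---|
| 198 (20% attrition) | 29% | 28% | 25% | 20% |
| 223 (10% attrition) | 32% | 31% | 28% | 22% |
| 248 (none lost) | 35% | 34% | 30% | 24% |

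**Step 5: other interaction sizes, 198 analysed, equal sexes.** 1.2 points: 11%. 3.6 points: 56%. About 4.8 points, twice the design effect: 80%.

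**Step 6: exaggeration when the condition is met.** At 198 with equal sexes and a true interaction of 2.4, the cut-off lies (3.34 − 2.4)/1.706 = 0.553 standard errors above the truth. The mean estimate beyond it is 2.4 + 1.706 × φ(0.553)/(1 − Φ(0.553)) = 2.4 + 1.706 × 0.342/0.290 = 4.4 points, nearly twice the true value. Significance in the wrong direction has probability below 0.1% and does not change this.

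**Step 7: what unconditional reporting would show.** With 99 of each sex, the arm effect within a sex has SE 6 × √(4/99) = 1.21 and a 95% CI of about ±2.4 points. That is imprecise, but the interval says so openly.

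**The case against.** The analysis is labelled exploratory and sits outside the main analyses. Sizing a trial for its main effect alone is normal, and exploratory interaction tests are routinely underpowered. Testing the interaction before looking within subgroups is a recognised guard against spurious subgroup claims. All of this stands: low power is not a design error here, and no larger sample is called for. It does not rescue the condition, however. The guard lies in relying on the interaction test and in cautious labelling, neither of which requires withholding estimates.

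Three stronger readings are tempting and are not supported.

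- A reader might infer that the sex question itself will go unreported. The text places its condition on the estimates by sex only. The interaction model is fitted in any case, and nothing says that its coefficient, interval or p-value will be withheld.
- A reader might infer that others would be left with nothing. The data-access section {31c} and Data Availability plan public code and a de-identified participant-level dataset. Sex is a stratification factor and a covariate, so it should be in that dataset and sex-specific effects should be recoverable.
- A reader might take power below 30% as a fixed property of the test. It depends on an assumed 2.4-point interaction and on 198 analysed. At the 10% attrition of the team's earlier trials, with 40% to 50% women, power is 31–32%; a 3.6-point interaction gives 56% even at 198 with equal sexes.

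It can also be said that tabulation is often left to an analysis plan, which is not shown. That would answer a complaint about missing detail, but here the protocol states a rule, and an analysis plan that followed it would carry the condition forward.

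**Conclusion.** The point holds as a fault in a reporting rule. Display of the sex-specific effects depends on a test with about 20–35% power for an interaction as large as the effect the trial was designed to find. They would therefore most likely stay hidden (about two times in three even at best) when such a difference exists, and would tend to be exaggerated when shown: about 4.4 points for a true 2.4 at 198 analysed with equal sexes.

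These figures rest on the assumed 2.4-point interaction, SD 6 in both sexes, 20% to 50% women and 198 to 248 analysed. A smaller interaction makes matters worse; only a much larger one, near 4.8 points at 198 with equal sexes, brings power to 80%. The weight is modest: the analysis is exploratory, the interaction test is still planned, and the primary result is untouched. The change is worth making because it is nearly free and serves a question to which the protocol gives priority.

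**What to change.** Replace the conditional sentence in Methods for additional analyses {20b} with wording such as: *From the model with the sex-by-arm interaction we will report the interaction estimate with its 95% confidence interval, and the difference between arms with its 95% confidence interval in men and in women, whatever the p-value. These results are exploratory.*

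The cost is one sentence and a table row. The model is already planned and sex is already a stratification factor, so no new data are needed, and the primary analysis and its type I error are unchanged. The small downside is that readers may over-read imprecise subgroup estimates; the exploratory label and the interaction interval printed beside them address that.
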